## Abstract

**Background:**

Although approximately 50% of Chinese with type 2 diabetes mellitus (T2DM) patients have vitamin D deficiency, studies regarding vitamin D supplementation on insulin resistance (IR) have mainly focused on non-Asians. Endurance exercise training (ET) enhances insulin-mediated glucose metabolism, which plays a critical role in T2DM prevention and control. However, the combined effects of vitamin D supplementation and ET on IR in T2DM patients are unclear. The objectives of this study is to investigate the synergistic effect of vitamin D supplementation combined with exercise training intervention on IR in T2DM patients.

**Methods and analysis:**

We propose a 3-month randomized controlled trial among 60 T2DM patients aged 40–65, newly diagnosed with T2DM ≤ 1 year, and with stable HbA1c level (≤ 8.0%) in the past 3 months. The participants will be randomly allocated to the vitamin D group, vitamin D combined with exercise training group, exercise training group, and control group (CG) using a computer-generated random number sequence. At baseline, participants will undergo a medical review, anthropometric measurements, dual X-ray absorptiometry, a 75-g oral glucose tolerance test (OGTT), ankle-brachial index measurements, and physical fitness measurements and will complete related lifestyle questionnaires. Fasting blood lipid and glucose levels were also measured. In a 3-month intervention period, vitamin D intervention group will receive a dose of 1000 IU daily; exercise group will perform a 1-h endurance exercise 3 times per week (maximal heart rate, 60–80%), and the control group will receive apparently identical tablets. Additionally, all participants will be advised to maintain their normal diet and physical activities during the intervention. All measurements will be repeated at 3-month follow-up after the intervention with the primary outcome measure expressed as a change from baseline in insulin sensitivity and secretion. Secondary outcome measures will compare the changes in anthropometry, ankle-brachial index, and physical fitness factors (e.g., peak oxygen uptake, hand grip strength). Data will be managed and analyzed using the Statistical Package for the Social Sciences.

**Discussion:**

This is the first study to conduct a randomized trial to clearly determine the independent and combined effects of vitamin D supplementation and endurance exercise trial on IR in Chinese T2DM patients as measured by OGTT. The findings from the proposed study will not only provide new evidences that vitamin D supplementation plays an important role in IR management but also develop a simple and efficient method to improve IR-associated metabolic diseases for T2DM patients.

**Trial registration:**

Chinese Clinical Trial Registry ChiCTR1800015383, Registered on 28 March 2018

## Introduction

With rapid social and economic developments during the past three decades, China is facing a growing threat from non-communicable chronic diseases (NCDs), with diabetes being considered one of the most common NCDs in China and several countries [1]. Diabetes prevalence in Chinese adults increased substantially from 0.67% in 1980 to 11.6% in 2010 and 10.9% in 2013 [2]. Insulin resistance (IR) is considered a prominent feature of type 2 diabetes mellitus (T2DM) and an important pathological and physiological basis for the development of T2DM [3]. How to effectively improve IR has become one of the emphases in the treatment of T2DM.

Vitamin D deficiency [25(OH)D < 20 ng/mL] is prevalent in several populations and has become a common public health problem worldwide due to sun protection measures, reduction of outdoor activities, increased obesity prevalence, and environmental pollution [4]. Zhang and colleagues recently reported that in China, 50% of T2DM patients were vitamin D deficient, further deteriorating their glucose tolerance status [5].

Mounting evidence suggests that altered vitamin D homeostasis may play a role in the development of IR and T2DM [6]. A prospective cohort study and meta-analysis indicated that subjects with 25-hydroxyvitamin D [25(OH)D] levels < 20 ng/mL were more likely to be diagnosed with T2DM compared to subjects with 25(OH)D levels ≥ 20 ng/ml [7]. However, to date, studies on vitamin D supplementation on IR in T2DM patients have mainly focused on non-Asian countries, and the results are inconsistent [8–13].

Krul-Poel et al. conducted a 6-month randomized controlled trial of vitamin D supplementation (50,000 IU/month) in 275 T2DM patients and found that glycated hemoglobin (HbA1c) levels did not improve in individuals with vitamin D < 20 ng/mL [8]. Similar results were also observed in 86 German T2DM patients with dose of 1904 IU/d for 6 months [9], while von Hurst et al. [14] found that 6 months of daily vitamin D supplementation could significantly reduce HOMA-IR values in vitamin D-deficient South Asian women living in New Zealand. The results were also supported by our previous study in Japanese adults [15]. The disparity may be partly attributed to the ethnicity-related differences in vitamin D receptor (VDR) polymorphisms (e.g., Apa I and Fok I) and insulin sensitivity [16, 17].

Documented evidence demonstrated that physical inactivity and obesity are two major risk factor for the development of T2DM; exercise intervention, where aerobic or resistance training or a combination, can exert many beneficial effects, such as increase fat oxidations, in the prevention and treatment of T2DM [18]. Exercise training not only increases energy consumption and reduces the accumulation of lipids in insulin-sensitive tissue such as the skeletal muscle [19] but also promotes glucose transportor-4 (GLUT-4) translocation and glucose uptake in skeletal muscle cells by activating AMP-activated protein kinase (AMPK) and downstream proteins of insulin-transmitting signals in skeletal muscle cells [20]. Additionally, recent studies have shown that exercise may also be involved in the regulation of vitamin D, which can increase VDR expression in skeletal muscle tissue and serum 25(OH)D levels [21–23]. Prior evidence suggested that in addition to regulating Ca^2+^ levels, vitamin D supplementation can directly upregulate the AMPK-GLUT-4 signaling pathway through VDR related (phosphorylated ERK1/2 and Mnk1) expression to increase glucose utilization and participate in exercise pathways of glucose utilization pathways [23]. These results suggested that vitamin D supplementation combined with exercise intervention may have a synergistic effect on the improvement of IR by activating different glucose utilization pathways. However, studies investigating the synergistic effect of vitamin D supplementation combined with exercise training intervention on IR in T2DM patients are relatively few [24].

In summary, this study aimed to (1) examine the effect of vitamin D supplementation on IR and (2) determine the synergistic effect of vitamin D supplementation combined with exercise training intervention on IR in Chinese T2DM patients with vitamin D deficiency by a randomized controlled trial.

## Methods and analysis

### Study design

The study is a randomized controlled trial with a 3-month intervention and 3-month follow-up period assessing the impact of combined vitamin D and exercise intervention on improving glucose and lipid metabolism in T2DM patients in Xi’an, China (34° N latitude). Vitamin D or placebo supplementation is designed as a double-blind trial. Sixty T2DM patients aged 40–65 years with serum 25(OH)D concentrations < 20 ng/mL on screening will be enrolled during winter and spring through posters and WeChat. Patients will be randomly assigned to either an intervention or a control group. The complete process is outlined in Fig. 1.

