### Randomization

All patients who give consent for participation and who fulfill the inclusion criteria will be randomized. An investigator who is independent of this study will randomly divide the subjects into four groups according to a computer-generated random allocation table stratified by age and sex. The treatment allocation code will be placed in an opaque envelope labeled with a sequential number. Group allocation was unknown to participants, investigators, and data collectors. The randomization code was broken after the last participant finished the study. The four groups are as follows: the placebo control group (CG), vitamin D supplementation group (VG), endurance exercise group (EG), and vitamin D supplementation combined endurance exercise group (VEG). All patients will be instructed not to change their levels of general physical activity and dietary habits during the intervention period. Their dietary changes will be recorded monthly as well.

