### Intervention procedure

#### Vitamin D intervention

Patients in the VG or VEG group will receive one tablet of vitamin D_3_ supplement (1000 IU/day, Nature Made, Otsuka Pharmaceutical Co, Ltd, Tokyo, Japan) immediately after meals to enhance absorption based on the guideline of Institute of Medicine for Vitamin D recommended [26], and patients in the EG or CG group will receive an identical appearance shape and color placebo as the vitamin D_3_ supplement every day for 3 months.

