#### Sunlight exposure

Participants will be instructed to record their outdoor activity time and exposed areas of the skin from 9 am to 5 pm for 7 consecutive days in a week using a questionnaire every month. A score to estimate the mean weekly sunlight exposure will be calculated, and additional details were published elsewhere [31].

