### Statistical analyses

Based on the relative studies on vitamin D intervention with IR [15], the sample size required for each group was estimated to be 12 with a power of 85%, and an effect size of 0.26 was assumed. Therefore, 48 T2DM patients are required. To account for 20% loss-to-follow-up, a total of 60 T2DM patients will be recruited. Power calculations will be performed using G*Power software version 3.1.9.2 [35].

Descriptive statistics will be calculated using mean (standard deviation) for continuous variables and *n* (%) for categorical variables. Differences will be compared using one-way analysis of variance (ANOVA) for continuous variables and chi-squared tests for categorical variables. Repeated measures ANOVA will be used to test the effect of vitamin D and exercise combined intervention on glucose and lipid metabolism, with adjustment for baseline levels of outcomes. A post hoc test with Bonferroni correction will be used to identify significant differences among the mean values when a significant main effect or interaction is identified. Finally, in the event of possible losses or dropouts, a statistical analysis will be performed by protocol and intention to treat. Data will be entered and cleaned using EpiData version 3.0 and managed and analyzed using the Statistical Package for the Social Sciences. Statistical significance will be set at *P* < 0.05.

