## Trial status

Active protocol version number: 1.3; January 1, 2019. The details of the protocol versions with the date of the amendment are provided in Table 3. Recruitment began on April 1, 2018. Currently, recruitment is ongoing and is expected to be completed in December 2020, and intervention and the last follow-up are expected to be completed in December 2021.

**Table 3 Tab3:** Protocol versions

Version	Date and changes
1.0	March 7, 2017, original protocol
1.1	March 1, 2018, introduction and background was improved
1.2	July 15, 2018, amendments of the inclusion and exclusion criteria
1.3	January 1, 2019, more comprehensive plan of the analysis was incorporated

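### Enrolment is confined to winter and spring but treatment and assessment are not, and the stated model has no term for season although serum 25(OH)D is a listed primary outcome

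*Protocol article*

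**What the plan says.** The Study design section of the protocol article describes a "randomized controlled trial with a 3-month intervention and 3-month follow-up period" in Xi'an, at 34° N, and states that eligible patients "with serum 25(OH)D concentrations < 20 ng/mL on screening will be enrolled during winter and spring through posters and WeChat". Table 2 places the intervention in weeks 1–12, the post-intervention assessment at week 13 and follow-up in weeks 13–24. Under Trial status, "Recruitment began on April 1, 2018", with recruitment expected to end in December 2020.

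Two arms (VG and VEG) take vitamin D. For the other two, "patients in the EG or CG group will receive an identical appearance shape and color placebo". The Randomization section has patients divided "according to a computer-generated random allocation table stratified by age and sex". The Statistical analyses section specifies a repeated measures ANOVA "with adjustment for baseline levels of outcomes". No other covariate is named.

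The article treats sun exposure as relevant to vitamin D in three places:
- The Introduction counts sun protection and less outdoor activity among the causes of deficiency.
- The exclusion criteria remove people with a history of sunbathing in the previous 6 months.
- The Sunlight exposure section has outdoor time and exposed skin recorded for one week each month: "A score to estimate the mean weekly sunlight exposure will be calculated". The Statistical analyses section gives this score no role.

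Table 1 lists serum 25(OH)D and 1,25(OH)₂D under primary outcomes, next to the insulin sensitivity and secretion indices.

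**The concern.** Restricting entry to winter and spring fixes the season in which deficiency is established. It does not fix the season in which tablet or placebo is taken, or in which the outcome is measured. A December entrant is treated and assessed before spring is under way. A late May entrant is treated almost wholly in June to August.

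If sunlight raises 25(OH)D, as the article's own rationale implies, the change from baseline in that outcome depends on entry date as well as on allocation. In a trial planned on 12 evaluable patients per arm, variation that is foreseeable and known at randomisation is then left in the error term. A chance difference in season mix between small arms also passes uncorrected into the estimate. Beyond this, some placebo patients may become less deficient during the course, which could narrow the contrast on which both aims depend.

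**Working it through.** **Inputs.** From the article: enrolment in winter and spring, a 12-week course, assessment at week 13, follow-up to week 24, recruitment from 1 April 2018, 60 patients in four groups, 48 evaluable. Assumed: winter and spring mean 1 December to 31 May, and entry is spread evenly over that window. The plan contains no figure for season to reproduce.

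**Step 1, dates.** Entry date plus 12, 13 and 24 weeks, in a non-leap year:

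| Entry | Course ends | Week 13 | Week 24 |
|---|---|---|---|
| 1 December | 23 February | 2 March | 18 May |
| 1 April | 24 June | 1 July | 16 September |
| 31 May | 23 August | 30 August | 15 November |

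The first recruitment day was itself 1 April, so the middle row is not hypothetical. If astronomical seasons are meant (21 December to 20 June), the course ends between 15 March and 12 September, and the conclusion is the same.

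**Step 2, how many patients.** There are 182 possible entry days from 1 December to 31 May. For 83 of them the 84-day course includes at least one day in June–August: 83/182 = 46%. For 41 of them more than half the course lies there: 41/182 = 23%. The spread in season is therefore not confined to a few late entrants.

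**Step 3, chance imbalance.** Assume 30 winter and 30 spring entrants, arms of 15, and allocation unrelated to entry date. The exact hypergeometric probability that the spring share differs by 20 percentage points or more is:
- 0.37 between two given arms of 15 (a gap of at least 3 patients);
- 0.20 between the pooled 30 vitamin D and 30 placebo patients (a gap of at least 6 patients).

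If the change in 25(OH)D differs by D ng/mL between spring and winter entrants, a gap of g in spring share shifts the unadjusted comparison by g × D. At g = 0.20 that is 0.2 ng/mL for every 1 ng/mL of D. The article gives no value for D, so the shift is left in that form.

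**Step 4, does the contrast shrink?** Write the mean change as T on tablet, S from sun and T + S + k on both.
- Vitamin D minus placebo in winter (no sun): T.
- Vitamin D minus placebo in summer: (T + S + k) − S = T + k.

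If the two sources add (k = 0), the contrast is unchanged and season contributes only variance. The contrast in 25(OH)D shrinks only if k < 0, that is, if the response flattens. The contrast in insulin resistance could also shrink if benefit depends on remaining below a threshold such as 20 ng/mL. The article gives neither k nor a dose-response curve.

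**Step 5, cost of a season term.** With 48 evaluable patients in four groups, a between-patient comparison has 48 − 4 = 44 error degrees of freedom. Baseline adjustment leaves 43 and a winter/spring indicator leaves 42.

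**The case against.** The strongest reply is that season is largely controlled already. Entry is limited to half the year, recent sunbathers are excluded, sunlight is recorded monthly, and patients are told to keep their habits. All four arms are randomised concurrently, so season is balanced in expectation. This stands. It rules out systematic bias, which the point does not claim, but it does not recover the precision lost to an omitted prognostic variable or correct a chance imbalance. The probabilities in step 3 would be lower if the allocation table is blocked, a detail that an article may leave out.

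A second reply is that covariate lists often belong to a fuller analysis plan, and that version 1.3 of the protocol is said to contain a more comprehensive one. That is fair, and the fuller plan may already include season. The article does, however, state both its stratification factors and its adjustment, and the change is cheap enough to make or confirm.

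A third is that a main effect for season removes variance but cannot restore a contrast that has been narrowed. This also stands, and it is why the by-season 25(OH)D table is needed as well as the covariate.

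A reader might infer more: that summer sun certainly dilutes the vitamin D effect, and that the planned 85% power is cut by a calculable amount. The document does not support either. It contains no seasonal 25(OH)D curve for Xi'an, no evidence of a plateau and no link from 25(OH)D to the size of the effect on insulin resistance. The season of the study behind the assumed effect size of 0.26 is not given either, so the 85% cannot be taken as the power in the absence of sun. Nor does the article claim that change within an arm up to week 24 shows persistence, so there is no such reading to correct.

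**Conclusion.** The point holds as a modest weakness in precision and interpretation. Treatment can run from deep winter to full summer and assessments from early March to mid-November, while neither the stated stratification nor the stated model contains season. Under even entry from December to May, about 46% of patients would have some treatment in June–August and about 23% would have most of it then. A gap of 20 points or more in season mix between pooled vitamin D and placebo patients has a probability of about 0.20 under the assumptions of step 3.

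The added variance is likely for 25(OH)D. For the insulin indices it is indirect and less certain. A narrower contrast is possible, but its size is unknown and no power figure should be attached to it. One reservation on scope: the model sentence in the Statistical analyses section refers to glucose and lipid metabolism, so its use for 25(OH)D is an inference from that outcome's listing as primary in Table 1.

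**What to change.** In the Statistical analyses section:

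1. Name season of enrolment as a prespecified baseline covariate alongside the baseline outcome level. A winter/spring indicator, with the months defined, is the simplest form. Calendar month at randomisation is the alternative: it costs one degree of freedom as a linear term and up to five as six categories. The randomisation date is fixed before treatment, so no new data are needed.
2. Report the week-13 difference in 25(OH)D between the vitamin D arms (VG and VEG) and the placebo arms (EG and CG), separately by season of enrolment, as a descriptive check on whether the contrast was maintained.
3. State that the monthly sunlight score is not a covariate in the primary model. It is measured after randomisation and may itself respond to the intervention, for example through changes in activity in the exercise arms.

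The cost is about one degree of freedom and one extra table. The by-season differences will be imprecise at this sample size and should not be tested formally. The change leaves enrolment, allocation and treatment as they are. Narrowing the enrolment window is not recommended: it would slow recruitment that is due to close in December 2020, for a gain that cannot be estimated from the document.

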**Fig. 1 Fig1:**
[figure not shown]
Study design flow chart. OGTT, oral glucose tolerance test; DXA, dual X-ray absorptiometry; VD, vitamin D; EG, endurance exercise group; VEG, vitamin D and endurance exercise group; CG, control group; MHR, maximal heart rate; ANOVA, analysis of variance

### Setting and participants

#### Inclusion and exclusion criteria

T2DM patients are eligible for study participation if they meet the following inclusion criteria: (a) patients newly diagnosed with T2DM ≤ 1 year, (b) patients with HbA1c level remaining stable at ≤ 8.0% in the past 3 months and patients with no plan of replacing the hypoglycemic agent in the near future, (c) patients without regular vitamin D and/or calcium supplements in the past year, (d) patients who do not meet the current National Physical Activity guidelines [25] in the past year, and (e) with stable body weight (≤ 2 kg variation in weight within the last 3 months.

The following participants were excluded: participants with acute infection; participants experiencing stress; participants experiencing the acute complications of diabetes; participants with heart, liver, and kidney insufficiency, osteoporosis and fracture, and metal implants in the body that could affect magnetic resonance imaging and dual-energy X-ray absorptiometry (DXA) measurements; and participants who have used insulin therapy and have history of sunbathing in the last 6 months.

The criteria for early termination of intervention are as follows: (a) blood calcium level is abnormally high (> 2.65 nmol/L), (b) serum 25(OH)D levels are abnormally high (> 100 ng/mL), and (c) have plan to replace with stronger blood glucose lowering drugs or HbA1c levels are > 8.5%.

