**Assessment**					
Blood parameter tests	X		X	X	
Body composition	X		X	X	
Ankle-brachial index	X		X	X	
Physical fitness factors	X		X	X	

Analysis of blood samples is as follows: a standard 75-g oral glucose tolerance test (OGTT) will be performed between 0830 and 1100 after a 12-h overnight fast, and venous blood samples will be collected in Venoject-II AutoSep tubes at time points 0, 30, 60, 90, and 120 min to determine the plasma glucose and serum insulin levels. Fasting serum sample will be used to measure the levels of 25(OH)D, 1,25(OH)_2_D, calcium, fasting glucose (*G*_0_), fasting insulin (*I*_0_), HbA1c, triglyceride, cholesterol, low-density lipoprotein, and high-density lipoprotein.

Primary outcomes are as follows: changes in insulin sensitivity and secretion.

Fasting blood glucose and insulin will be used to calculate the insulin resistance index (Homeostatic Model Assessment of Insulin Resistance [HOMA-IR]) and β cell secretion index as follows: HOMA-IR = *G*_0_ × *I*_0_/22.5 and HOMA-β = 20 × *I*_0_/(*G*_0_ – 3.5).

Insulin sensitivity estimated using the Matsuda index of insulin sensitivity during the OGTT will be calculated as follows: 1000/square root of ([*G*_0_ × *I*_0_]) × (mean OGTT glucose concentration × mean OGTT insulin concentration) [27]. Early phase of insulin secretion will be estimated using the insulinogenic index as follows: *I*_30_–*I*_0_/*G*_30_ – *G*_0_ (△I30/△G30), where *I*_30_ and *G*_30_ represent insulin and glucose values at 30 min during the OGTT, respectively [28]. The increments in the area under the curves during the complete 120-min period of the OGTT will be calculated using the trapezoid rule to assess the total changes in glucose and insulin levels [22].

Secondary outcomes are as follows: changes in anthropometry, metabolic indices, ankle-brachial index, and physical fitness factors

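### The calcium limit for early termination is printed in nmol/L; the unit must be mmol/L

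*Protocol article*

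**What the plan says.** The last paragraph of Inclusion and exclusion criteria opens with "The criteria for early termination of intervention are as follows" and gives three items.

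- Item (a): "blood calcium level is abnormally high (> 2.65 nmol/L").
- Item (b): "serum 25(OH)D levels are abnormally high (> 100 ng/mL").
- Item (c): a plan to move to stronger glucose-lowering drugs, or HbA1c above 8.5%.

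On measurement, the section Outcome measures and measurement procedures says only this: "Fasting serum sample will be used to measure the levels of 25(OH)D, 1,25(OH)_2_D, calcium", followed by the other analytes. It gives no unit for calcium. The only other mentions of calcium are the mechanism paragraph of the Introduction and the eligibility criterion on calcium supplements. Neither carries a unit or a limit.

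**The concern.** A limit meant to pick out abnormally high calcium must lie above the values most people have. In nmol/L, 2.65 lies far below any calcium value a living participant could have, so the number and the words of item (a) cannot both be right.

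What is at stake is the usability of a safety criterion. Two of the four arms receive vitamin D daily for 3 months, and item (a) is the article's only numeric rule tied to calcium. Site staff, an ethics committee or a team reusing the protocol should be able to apply it without guessing the unit. The statistical analysis is not at stake.

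**Working it through.** **Inputs from the article**

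- Printed calcium limit: 2.65 nmol/L (Inclusion and exclusion criteria, item (a)).
- 25(OH)D limit: 100 ng/mL (item (b)); participants enter "with serum 25(OH)D concentrations < 20 ng/mL on screening" (Study design).
- HbA1c limit: 8.5% (item (c)); entry requires 8.0% or less.
- Planned size: "a total of 60 T2DM patients will be recruited" (Statistical analyses).

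**Inputs not in the article**

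- Blood calcium of about 2.0 to 2.7 mmol/L. This is an assumption, used for illustration only.
- Atomic weight of calcium 40.08 g/mol, a physical constant.

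**Step 1: convert the printed limit.** 1 mmol/L = 10^6 nmol/L, so 2.65 nmol/L = 2.65 / 10^6 = 0.00000265 mmol/L. In mass units this is 0.00000265 × 40.08 / 10 ≈ 0.0000106 mg/dL.

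**Step 2: compare with possible values.** The assumed range of 2.0 to 2.7 mmol/L is 2,000,000 to 2,700,000 nmol/L. Every value in it exceeds 2.65 nmol/L, so read literally all 60 planned participants would meet item (a) at their first calcium result. The assumed range does not drive this: the same holds for any calcium above 0.00000265 mmol/L.

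**Step 3: apply the corrected unit.** 2.65 mmol/L = 2.65 × 40.08 / 10 ≈ 10.6 mg/dL. Within the assumed range, results from 2.0 to 2.65 mmol/L do not trigger the criterion and results above 2.65 mmol/L do. That matches what the clause says it is for.

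**Step 4: compare with the neighbouring criteria.**

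| Item | Limit | Entry requirement | Can it separate raised from ordinary values? |
|---|---|---|---|
| (a) calcium, as printed | > 2.65 nmol/L | none stated | No, every value exceeds it |
| (a) calcium, in mmol/L | > 2.65 mmol/L | none stated | Yes |
| (b) 25(OH)D | > 100 ng/mL | < 20 ng/mL | Yes, at five times the entry ceiling (100 / 20) |
| (c) HbA1c | > 8.5% | ≤ 8.0% | Yes |

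Items (b) and (c) work as limits. Only item (a) fails as printed.

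**The case against.** The strongest reply is that the misprint corrects itself. The clause says the level must be abnormally high, and 2.65 makes sense for blood calcium in only one molar unit. The measures are carried out in hospital by specialist doctors, and a qualified practitioner discusses any abnormality with the participant (Safety and adherence considerations). Nobody is likely to stop all 60 participants. This stands, and it is why the point is minor.

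A second reply concerns the schedule. Table 2 marks blood tests at baseline, after the intervention and at follow-up, with none in weeks 1–12. The section Follow-up visits puts the post-treatment assessment in the last week of treatment, which changes little. On that schedule, neither the printed nor the corrected limit would stop much treatment unless further samples are taken. That is fair as a comment on practical effect. It is a separate matter from the unit, and an article may leave interim safety bloods to the full protocol.

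A third reply is that the article condenses a protocol that is not shown. The document used at the site may carry the right unit, and a fault in reading the text from the page cannot be wholly excluded. The surrounding text is intact, however, with no gap or redaction, and the article as available states the limit wrongly.

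None of these replies makes nmol/L correct.

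**Conclusion.** The concern holds as a minor error. The printed limit is too low by a factor of 10^6 compared with the same number in mmol/L, and it contradicts the wording of its own clause. That conclusion needs only the unit conversion and the fact that real blood calcium exceeds 0.00000265 mmol/L. Reading mmol/L as the intended unit rests on the assumed ordinary range of about 2.0 to 2.7 mmol/L, since the article gives no calcium values. The consequence is confined to the printed text of one individual early-termination criterion. Sample size, power, estimand and analysis are untouched.

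**What to change.** In item (a) of the early-termination criteria, under Inclusion and exclusion criteria, replace nmol/L with mmol/L so that the limit reads > 2.65 mmol/L. Before issuing the correction, confirm the laboratory's reporting unit; if it reports in mg/dL, state the equivalent of about 10.6 mg/dL. Check that the full protocol and site documents carry the same unit.

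The cost is a one-letter correction, with no new procedure, visit or blood draw.

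### High blood calcium ends the intervention, but no entry criterion limits it, so a patient can be randomised while already meeting that termination criterion

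*Protocol article*

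**What the plan says.** The Inclusion and exclusion criteria section of the protocol article lists three grounds for ending the intervention early:

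- (a) "blood calcium level is abnormally high", with the limit printed as > 2.65 nmol/L (unit as printed);
- (b) "serum 25(OH)D levels are abnormally high (> 100 ng/mL";
- (c) "have plan to replace with stronger blood glucose lowering drugs or HbA1c levels are > 8.5" percent.

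None of the three carries a time window or a change-from-baseline condition.

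On entry, Study design requires "serum 25(OH)D concentrations < 20 ng/mL on screening". The inclusion list requires a stable HbA1c of at most 8.0% and no plan to replace the glucose-lowering agent. It also rules out regular vitamin D or calcium supplements in the past year. The exclusions include "participants with heart, liver, and kidney insufficiency, osteoporosis and fracture, and metal implants in the body". Neither list gives a blood calcium level or names hypercalcaemia.

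The Randomization section says: "All patients who give consent for participation and who fulfill the inclusion criteria will be randomized". Under Outcome measures and measurement procedures, the sentence that begins "Fasting serum sample will be used to measure the levels of 25(OH)D" goes on to include calcium. Table 2 places blood tests at week 0, at week 13 after the intervention, and in the follow-up period.

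**The concern.** A termination criterion describes a state in which the plan does not want the intervention to continue. If the same state can exist at entry and nothing there keeps such a patient out, the plan can start an intervention that its own rule says to end. Two of the three triggers cannot be met by a patient who was correctly enrolled. The calcium trigger can.

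Two things are at stake. One is safety: a patient above the plan's own calcium limit could be allocated to an arm that receives vitamin D. The other is a foreseeable departure from the assigned intervention, in a small trial, that a value already being collected could prevent.

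**Working it through.** The plan gives no figure on raised calcium, so there is none to reproduce. The check is mainly a comparison of the passages.

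**Step 1. Match each termination trigger to its entry counterpart.**

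| Termination trigger | Entry counterpart | Can an eligible patient meet it at week 0? |
|---|---|---|
| 25(OH)D > 100 ng/mL | 25(OH)D < 20 ng/mL at screening (Study design) | No |
| HbA1c > 8.5%, or a planned stronger drug | HbA1c ≤ 8.0%, and no plan to replace the agent (inclusion criterion b) | No |
| Blood calcium above the stated limit | No blood level; supplement use (inclusion criterion c) and kidney insufficiency (exclusion) only | Yes |

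**Step 2. Is the value available at week 0?** Yes. Calcium is in the fasting panel and Table 2 marks blood tests at week 0. The measurement exists; what is missing is a link from it to eligibility. Table 2 puts screening, randomisation and these blood tests in the same week-0 column, so it does not show whether the result is seen before allocation.

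**Step 3. Does another passage close the gap?** Safety and adherence considerations says that abnormalities found at screening or baseline are discussed promptly with the participant by a qualified practitioner. That neither excludes the patient nor holds back allocation. Table 2 schedules no blood test in weeks 1 to 12, so week 0 is the only scheduled calcium value before the end of the intervention.

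**Step 4. How many patients?** Inputs: 60 patients recruited (Statistical analyses) and four arms, two of them with vitamin D (Intervention procedure). I assume equal groups, so 60 × 2/4 = 30 patients receive vitamin D. The proportion p of otherwise eligible candidates above the limit is not in the documents; 0.5% to 2% is an assumption.

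Expected number = n × p. Chance of at least one = 1 − (1 − p)^n.

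| p (assumed) | Expected of 60 | At least one of 60 | Expected of 30 on vitamin D | At least one of 30 |
|---|---|---|---|---|
| 0.5% | 0.3 | 1 − 0.995^60 = 26% | 0.15 | 1 − 0.995^30 = 14% |
| 1% | 0.6 | 1 − 0.99^60 = 45% | 0.3 | 1 − 0.99^30 = 26% |
| 2% | 1.2 | 1 − 0.98^60 = 70% | 0.6 | 1 − 0.98^30 = 45% |

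The expected counts are the fairer summary. The chance of at least one looks large only because it accumulates over 60 people. The supplement and kidney criteria would lower p by an unknown amount.

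**The case against.** The strongest reply is that this is an omission in a condensed article, not a contradiction. Criteria for ending an intervention apply once it has begun, and no passage says that the week-0 value is tested against them. No passage requires every termination trigger to have an entry limit either; the 25(OH)D and HbA1c entry limits may be there simply to define a deficient, stable population. The full protocol may hold a calcium criterion, since Table 3 records that version 1.2 amended the eligibility criteria.

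Part of this stands. The passages do not flatly conflict, and a fuller list may exist. But the article prints an itemised eligibility list directly before its termination list, and the two do not fit for one trigger of three. The termination rule has no time condition, and the Randomization section makes allocation follow from eligibility. Someone following the text has no instruction to act on a high week-0 calcium before allocation.

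A reader might also infer more than the documents support:

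- *That the entry criteria ignore calcium altogether.* They do not. Calcium supplement use and kidney insufficiency are both covered; only the blood level is not.
- *That such a patient uses up part of the 20% loss-to-follow-up allowance.* The rule ends the intervention, not the assessments, and Statistical analyses plans an intention-to-treat as well as a per-protocol analysis. Stopping the intervention is not the same as missing data.
- *That the arms would be biased.* A week-0 value precedes allocation and the rule applies in all four arms, so no systematic difference between arms follows.
- *That the point comes down to the printed unit or the lack of blood tests during the intervention.* Those are separate matters. Settling either would still leave entry without a calcium level.

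**Conclusion.** The point holds as a gap between the entry and termination criteria. High blood calcium is the only one of the three triggers that an eligible patient can already meet at week 0, and the article does not tie the week-0 value to allocation. The consequence is a possible allocation, including to the two vitamin D arms, of a patient who already meets criterion (a), and an avoidable discontinuation of the intervention.

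The numbers are small: about 0.3 to 1.2 of 60 patients, and 0.15 to 0.6 of 30 on vitamin D. These rest on an assumed prevalence of 0.5% to 2% and on equal groups. The mismatch itself does not depend on the prevalence. It does rest on the article's lists being the operative criteria. The case for acting is safety and the very low cost of the remedy, not a threat to the trial's comparison.

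**What to change.** Reconcile the entry and termination lists in the Inclusion and exclusion criteria section so that a patient who already meets a termination criterion at week 0 is not randomised. State in the Randomization section that allocation follows review of the week-0 calcium result. If the full protocol already does this, the article should say so. The limit itself is for the sponsor's clinicians to set; none is proposed here.

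The cost is about one line of eligibility text. No new test is needed, because calcium is already in the week-0 panel. The downside is that allocation waits for that result and an occasional candidate is not enrolled.
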